### Recruitment {15}

Advertisement for recruitment will be posted on medias, like Wechat, Weibo, and Tiktok, so that any potential subjects will be reached. The recruitment of subjects was estimated to be completed in 2 years.

## Assignment of interventions: allocation

### Sequence generation {16a}

A computer-based Interactive Web Response System (IWRS) will be adopted. Randomization will be stratified by centers.

### Concealment mechanism {16b}

Authorized physicians followed corresponding treatments for enrolling subjects based on grouping information sent from IWRS.

### Implementation {16c}

Authorized physicians will generate the allocation sequence, enroll participants, and assign participants to interventions.

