### Who will obtain informed consent? {26a}

Authorized physicians will obtain informed consent from the subjects before randomization.

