## Assignment of interventions: blinding

### Who will be blinded {17a}

Physicians and patients will not be blinded after assignment to interventions. However, all endpoints and events that occur after randomization will be adjudicated by an independent clinical events committee who is blinded to the study. Furthermore, data analysts will be blinded.

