### Procedure for unblinding if needed {17b}

The design is open label, with only outcome assessors being blinded, so unblinding of the procedure will not occur.

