### Data management {19}

Both paper-based case report form (CRF) and EDC will be used in this study. CRF will be completed by authorized and trained physicians according to their medical history. It will be double checked by another physician relevant to this study. The paper-based CRF will be stored in the trial office securely. Then, the data will be entered into the database by authorized physicians for screening and randomization purposes.

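### The Implementation section gives sequence generation to the recruiting physicians, which conflicts with the IWRS allocation described just before it and leaves concealment uncertain

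*Protocol article*

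**What the plan says.** Three consecutive sections of the protocol article deal with allocation.

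- The first, on sequence generation {16a}, states: "A computer-based Interactive Web Response System (IWRS) will be adopted". It adds that centre is the stratification factor.
- The second, on the concealment mechanism {16b}, has only this to say: "Authorized physicians followed corresponding treatments for enrolling subjects based on grouping information sent from IWRS".
- The third, on implementation {16c}, gives the roles as follows: "Authorized physicians will generate the allocation sequence, enroll participants, and assign participants to interventions".

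The same role appears twice more at the point of entry. The section on informed consent {26a} states: "Authorized physicians will obtain informed consent from the subjects before randomization". Under Data management {19}, after the paper form is completed and checked, "the data will be entered into the database by authorized physicians for screening and randomization purposes".

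On blinding, Who will be blinded {17a} says "Physicians and patients will not be blinded after assignment to interventions", and Procedure for unblinding if needed {17b} says "The design is open label, with only outcome assessors being blinded". The former section adds that data analysts are also blinded.

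**The concern.** Allocation concealment means that whoever decides whether a subject enters the trial cannot know, before that decision is fixed, which arm the subject would get. It is a separate matter from blinding, and an open-label trial depends on it heavily because nothing after assignment is hidden at the site.

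A person who generates a sequence can know what comes next. The Implementation sentence gives generation to the role that enrols and assigns. With that knowledge, a physician could approach, delay or pass over a subject according to the arm on offer. The trial weighs ischaemic benefit against bleeding, and physicians will have a view on both risks for a given patient. Selective entry on either risk would make the arms differ at baseline in the characteristics that drive the endpoints.

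The safeguards that the article names act later. The blinded events committee classifies events after randomization, and the intention-to-treat rule keeps subjects in the arm they were assigned to. Neither restores comparability if the assignment was influenced. The section on additional analyses plans no adjusted analyses, so baseline differences would not be addressed there either.

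**Working it through.** No arithmetic applies. The point turns on who generates the sequence and who can see it, and it does not depend on the sample size, power, alpha or event count. The check is to set the sections side by side.

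1. **Who generates the sequence?** Sequence generation {16a} names only the IWRS. Implementation {16c} names authorized physicians. These are different answers to the same question.

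2. **Who makes the assignment?** In Concealment mechanism {16b}, physicians receive the group from the IWRS and act on it. In Implementation {16c}, physicians assign. These two can be reconciled if assigning means requesting randomization in the system and carrying out the result. The statement on generation in step 1 cannot be reconciled in that way.

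3. **What else does that role do?** It obtains consent before randomization {26a} and enters the data used for screening and randomization {19}. So the role said to generate the sequence also works at the entry step, where foreknowledge matters.

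4. **Is there judgement at entry?** Intervention description {11a} requires subjects to be event-free and compliant with DAPT at 12 months (± 1 month), with no interruption of more than 14 days. These criteria are fairly objective. Discretion remains in whom to approach, when within the window, and through consent.

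5. **Does anything else name an independent generator or holder?** No. The Data and Safety Monitoring Board and the steering committee both include biostatisticians, but neither is given the sequence. Concealment mechanism {16b} says what physicians do once they have the group. It does not say that the sequence is hidden from them until then.

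6. **Does the open-label design matter?** It is context, not a second error. Past assignments are visible at each site, so concealment of future ones must come entirely from how the sequence is generated and held.

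7. **Is this a detail that an article may leave to the full protocol?** No. Silence on who generates the list could be excused. Here the article makes a positive statement, in current text, that conflicts with its neighbours.

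Two outcomes follow:

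| Which text governs | Who can know the next assignment | Consequence |
|---|---|---|
| Implementation {16c} as written | The recruiting role | Concealment not protected; selection at entry possible |
| {16a} and {16b}, with the IWRS holding the list until a subject is registered | No one at the site, from the list itself | Concealment kept; {16c} is a misstatement |

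**The case against.** The strongest reply is that two of the three allocation sections point to a central system. The Implementation section is a single sentence answering a checklist item, and its author may simply have meant that physicians trigger randomization in the IWRS. The data-management text, in which physicians enter data for that purpose, fits this. On that reading nothing is wrong with the randomization itself.

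This stands to the extent that an actual loss of concealment is not shown. It does not remove the point, because the sentence says plainly that physicians generate the sequence, and no other section corrects it. Sites may follow the text, and a reader judging the randomization would have to take it at face value.

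Three stronger readings are tempting, and the documents do not support them:

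- **That concealment is already lost.** This holds only if the Implementation sentence governs over the two IWRS sections.
- **That one individual generates the list, judges eligibility, prescribes and reports events.** The text assigns tasks to a role spread over approximately 30 sites. Drugs are prescribed in outpatient departments and events are reported by physicians generally. Nothing shows that the same people do all of it. The overlap of generation, enrolment and assignment in one role is enough for the point.
- **That the bias can be given a number.** The documents contain nothing from which to derive how many assignments would be foreseen or how many subjects steered.

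**Conclusion.** Wrong as written. Implementation {16c} contradicts Sequence generation {16a} and Concealment mechanism {16b} on who generates the allocation sequence. That conflict is certain from the text.

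The consequence is conditional. If {16c} is followed, upcoming assignments could be known to recruiters in an open-label trial, and the resulting selection bias could not be repaired by blinded adjudication or by intention-to-treat analysis. If {16a} and {16b} describe practice, and the IWRS withholds the list until a subject is registered, the trial is sound on this point and only the sentence is at fault.

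No numerical size is attached. In scope, the rule concerns the assignment of every randomized subject, planned at 1624. No sample size or power figure changes. The matter deserves correction before the first randomization, because concealment cannot be restored for subjects already assigned.

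**What to change.** Rewrite Implementation {16c} along these lines: *The sequence, stratified by centre, is generated and held by the IWRS provider or by a statistician with no role in recruitment or care. Physicians confirm eligibility and consent in the IWRS, enrol the subject, and only then receive the assignment from the system.*

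Add to Concealment mechanism {16b} that the sequence is hidden from all site staff until eligibility and consent have been recorded for the subject concerned. If a statistician is chosen over the provider, it should not be one of the analysts who are to be blinded.

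The cost is wording, plus a check that the IWRS is set up in this way. The system is already planned, and Trial status says that the study has not yet begun. If the IWRS already works like this, the correction only brings the text into line with practice.

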## Assignment of interventions: blinding

### Who will be blinded {17a}

Physicians and patients will not be blinded after assignment to interventions. However, all endpoints and events that occur after randomization will be adjudicated by an independent clinical events committee who is blinded to the study. Furthermore, data analysts will be blinded.

### Procedure for unblinding if needed {17b}

The design is open label, with only outcome assessors being blinded, so unblinding of the procedure will not occur.

## Data collection and management

### Plans for assessment and collection of outcomes {18a}

An electronic data capture (EDC) system will be used to collect study data. All baseline characteristics, clinical events, and outcomes will be reported to an independent committee. The committee members will be capable of assessing the information blindly. Subjects are mandatorily followed up regularly so necessary information can be acquired.

### Plans to promote participant retention and complete follow-up {18b}

Appropriate medical advice can be provided to subjects just in time through message or phone call if they adhere to the protocol and complete follow-up. To those who would be willing to take office visits, proper compensation will be provided. Subjects who suffer from any events or deviate from the protocol will be excluded from the study. However, they will still be monitored and cared for until the end of the study.

### Data management {19}

Both paper-based case report form (CRF) and EDC will be used in this study. CRF will be completed by authorized and trained physicians according to their medical history. It will be double checked by another physician relevant to this study. The paper-based CRF will be stored in the trial office securely. Then, the data will be entered into the database by authorized physicians for screening and randomization purposes.

### Confidentiality {27}

All information collected in this study will be strictly protected. Personal information about subjects including results of laboratory tests and procedural findings will be restricted in each center. Only those who is authorized by principle investigators can access the data. Subjects will be allocated an individual trial identification number and stored on a secure database to protect confidentiality before, during, and after the trial.

### Plans for collection, laboratory evaluation, and storage of biological specimens for genetic or molecular analysis in this trial/future use {33}

Biological specimens collected from subjects will be used only for laboratory testing and will be destroyed safely when the study ends. No genetic or molecular analysis is scheduled.

## Statistical analysis

### Statistical analysis of primary and secondary outcomes {20a}

All analyses will be performed on the intention-to-treat (ITT) population. The primary and secondary endpoints that are related to the time to an event will be assessed with Cox survival analysis. The primary analyses will compare the time to event from 12 to 36 months postprocedure between subjects randomized to 36 and 12 months DAPT using the stratified log-rank test. Kaplan‒Meier estimates of MACEs and other endpoints, as well as the 2-sided 95% confidence interval (CI) of the treatment difference in Kaplan‒Meier rates, will be presented for each treatment arm. Other secondary endpoints will be analyzed with the chi-square test or Fisher’s exact test for frequent comparisons. The two-sided significance level will be fixed at 5%. All tests will be performed with SAS version 9.4 (SAS Institute Inc., Cary, North Carolina, US).

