### Intervention description {11a}

All subjects will take a loading dose of 300 mg clopidogrel or 180 mg ticagrelor plus 300 mg aspirin within 24 h before intervention. After the index procedure, a daily dose of a P2Y12 inhibitor (75 mg clopidogrel per day or 180 mg ticagrelor twice a day) as well as 100 mg aspirin per day will be administered over 12 months after the index procedure (observational period). Aspirin can be replaced by cilostazol (50 mg twice a day) or indobufen (100 mg twice a day) if subjects have a history of a gastric ulcer or bleeding. For the subjects who are eligible for randomization at 12 months (± 1 month), the prerandomization daily dose of the P2Y12 inhibitor will be continued or discontinued based on the randomization arm. Aspirin will be maintained for the duration of treatment. Subjects who switch from one type of P2Y12 inhibitor to another are eligible for enrollment if they have not changed within 6 months before randomization. All drugs will be prescribed to subjects routinely at the outpatient department of each center. Regular records of drug usage will be made throughout the entire study by investigators. Compliance will be reviewed by phone calls to subjects every 3 months from physicians to reconfirm the daily dose of each drug. Prasugrel has not yet been approved for the treatment of coronary artery disease in China.

All XINSORB BRS-treated subjects who are receiving 12 months (± 1 month) of the DAPT post index procedure and who are event-free (from death, MI, stroke, repeat revascularization, scaffold thrombosis, and BARC type 3 or 5 bleeding events) and who are compliant with DAPT (defined as no interruption more than 14 days) are eligible for randomization. The subjects will be randomized at a 1:1 ratio to receive either aspirin alone or a continuation of DAPT for an additional 24 months.

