#### Follow-up

All randomized subjects will be followed up for 24 months after randomization. The subjects who are randomized to the prolonged DAPT arm will receive a daily dose of a P2Y12 inhibitor and aspirin for a total of 3 years (± 1 month). The other subjects will receive aspirin alone. All subjects will be contacted at 3, 6, 9, 12, 15, 18, 21, 24, 27, 30, 33, and 36 months through a phone call or office visit. Demographic, clinical, and procedural information at the time of enrollment as well as subsequent clinical endpoints, serious adverse events, concomitant medications, and antiplatelet therapy compliance will be obtained. Data will be continuously collected until the end of the study. All endpoints and events that occur after randomization will be adjudicated by an independent clinical events committee who is blinded to the study.

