### Outcomes {12}

The primary endpoint of this study is the incidence of the composite endpoint, including all-cause death, any MI, and all revascularizations (major adverse cardiac events, MACEs) 24 months after randomization. MIs will be classified and adjudicated according to the Academic Research Consortium (ARC) definitions [16].

The secondary endpoints of the study include the device-oriented composite endpoint (DoCE) of TLF (cardiac death, target vessel-related myocardial infarction [TV-MI], or ischemia-driven target lesion revascularization [ID-TLR]), target vessel failure (TVF; cardiac death, MI, or ischemia-driven target vessel revascularization [ID-TVR]), the individual component endpoints of these endpoints, and scaffold thrombosis. Scaffold thrombosis will be defined as acute (< 24 h), subacute (1 to 30 days), late (30 days to 1 year), and very late (beyond 1 year), and the level of evidence (definite or probable) will be based on the ARC definitions [16].

Bleeding events are the secondary endpoint. BARC type 3 or 5 bleeding events at major bleeding events will include fatal bleeding, intracranial hemorrhage, cardiac tamponade, any transfusion with overt bleeding, a reduction in hemoglobin greater than 3 g/dl, and bleeding requiring surgery (excluding dental, nasal, skin, and hemorrhoid surgeries).

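### The primary comparison is placed on a postprocedure clock (months 12 to 36), while the endpoint and follow-up run 24 months from a randomization at 12 ± 1 months

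*Protocol article*

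**What the plan says.** Four places in the protocol article set the timing of the primary result.

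- **Statistical analysis of primary and secondary outcomes {20a}**: the primary stratified log-rank comparison is of "time to event from 12 to 36 months postprocedure". The same section opens with "All analyses will be performed on the intention-to-treat (ITT) population". It plans Kaplan-Meier estimates and a confidence interval for their difference, without naming a time point.
- **Outcomes {12}**: the primary composite is all-cause death, any MI and "all revascularizations (major adverse cardiac events, MACEs) 24 months after randomization".
- **Follow-up**: "All randomized subjects will be followed up for 24 months after randomization". Treatment in the prolonged arm ends at a "total of 3 years (± 1 month").
- **Intervention description {11a}**: the timing rule reads "For the subjects who are eligible for randomization at 12 months (± 1 month"). Subjects must by then be "event-free (from death, MI, stroke, repeat revascularization, scaffold thrombosis, and BARC type 3 or 5 bleeding events").

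Section {20a} does not name randomization as time zero, does not call 12 and 36 nominal times, and does not mention delayed entry.

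**The concern.** The sentence that governs the primary test uses a different origin and a different end from the endpoint it is meant to test. If it is programmed as written, three things follow.

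- **Randomized before month 12.** An event between randomization and month 12 happened under allocated treatment but lies outside the window. The subject then contributes nothing to the comparison, which is at odds with the ITT statement in the same section.
- **Randomized after month 12.** The interval from month 12 to randomization is event-free by the eligibility condition. Unless entry is delayed to the randomization date, it is counted as time at risk.
- **Also randomized after month 12.** Events after month 36 but within 24 months of randomization belong to the endpoint in {12} and are cut off by {20a}.

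Two analysts could therefore report two different primary results from the same data, each citing the protocol.

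**Working it through.** **Inputs from the protocol article.** Randomization at months 11 to 13 ({11a}). Endpoint and follow-up of 24 months from randomization ({12}, Follow-up). Analysis window of months 12 to 36 ({20a}). Assumed MACE rates of 6.5% (standard) and 3.5% (prolonged), 649 per arm before loss and 812 per arm randomized, 1-sided alpha 2.5% (Sample size {14}).

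**Assumptions not in the article.** Randomization time R is uniform on months 11 to 13. The hazard is constant in each arm. The 6.5% and 3.5% apply to the 24 months after randomization.

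**The plan's own figures.** The article gives no figure for the effect of the window, so there is none to reproduce. The inflation 649/0.8 = 811.25, hence 812, does reproduce. The 649 itself does not reproduce at 1-sided 2.5% (Schoenfeld gives 780 for a hazard ratio of 0.530). That is a separate matter on which this point does not depend.

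**Step 1: hazards.** λ = −ln(1 − p)/24 per month.
- Standard: −ln(0.935)/24 = 0.00280
- Prolonged: −ln(0.965)/24 = 0.00148
- Hazard ratio: ln(0.965)/ln(0.935) = 0.530

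**Step 2: share of follow-up outside the window.** This is |R − 12|/24. Its mean is 0.5/24 = 2.1% and its maximum is 1/24 = 4.2%.

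**Step 3: events inside the window.**
- For R < 12 the probability is exp(−λ(12 − R)) − exp(−24λ).
- For R > 12 it is 1 − exp(−λ(36 − R)).
- At R = 11 this gives 0.0622 (standard) and 0.0335 (prolonged), against 0.0650 and 0.0350 on the randomization clock.

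Expected events at 812 per arm, with Schoenfeld power Φ(√d·|ln HR|/2 − 1.96):

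| Window | Events d | Lost | Power |
|---|---|---|---|
| 24 months from randomization | 812 × 0.100 = 81.2 | – | 81.6% |
| Months 12–36, R uniform | 79.5 | 1.7 (2.1%) | 80.8% |
| Months 12–36, all at month 11 | 77.7 | 3.5 (4.3%) | 79.9% |
| Months 12–36, all at month 13 | 77.9 | 3.3 (4.1%) | 80.0% |

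With 649 per arm in place of 812, events go from 64.9 to 63.5 and power from 72.5% to 71.6% (70.6% if all are randomized at month 11). The shares lost are the same.

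**Step 4: pre-randomization time counted.** The mean of max(R − 12, 0) is 0.25 month, or 0.25/24 = 1.0% of the window. The maximum is 1 month, or 4.2%.

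**Step 5: effect on the comparison.** A simulation of 2 million subjects per arm compared the two clocks, using events divided by person-time with no delayed entry. The hazard ratio was 0.530 on both. The literal window lowered the event rate by about 1.1% in each arm. With equal hazards the ratio was 0.995 on the randomization clock and 0.994 on the literal window.

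**Step 6: the end of the curve.** At month 35 + x, subjects still within their 24 months have R > 11 + x, a share of (2 − x)/2. Apart from other losses, this falls from 100% at month 35 to 50% at month 36 and averages 75%.

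**The case against.** The strongest reply is that 12 and 36 are nominal labels. Eligibility criteria {10} names the arms by 12 and 36 months in total straight after allowing ± 1 month at randomization. Follow-up puts the same tolerance on the 3-year end of treatment. The {20a} sentence itself uses 36 and 12 months as arm names. On that reading the window means randomization to 24 months later and nothing is lost. The reading is plausible, which is why every consequence above is conditional. It does not remove the mismatch: elsewhere the article writes the tolerance beside the number, whereas {20a} gives none and names the procedure as the anchor.

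A second reply is that the time origin and censoring rule are usually left to the analysis plan. Leaving them out would indeed be no finding. Here, however, the article states a window, and it differs from the one in its own endpoint.

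Three stronger readings are tempting, and the document does not support them.

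- **Immortal-time bias.** Allocation is 1:1 and randomization timing should not differ by arm, so the pre-randomization time and the excluded events fall on both arms alike in expectation. The hazard ratio does not move under constant hazards.
- **A larger loss because risk rises just after the P2Y12 inhibitor is stopped.** If that were so, the loss could exceed 2% and could differ between arms. The article gives no figure for such a rise, so no size can be attached to it.
- **A last month of the curve that rests on half the subjects.** Only the final instant does; the average is about 75%. Section {20a} also does not state that a 36-month Kaplan-Meier rate will be reported.

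**Conclusion.** The point holds as an inconsistency in the definition of the primary analysis window, with a small numerical effect. The {20a} window and the 24-month endpoint coincide only for randomization at exactly month 12.

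Read literally, {20a} would lose about 2% of events (at most about 4%), and about 0.8 power points (at most 1.7) at 812 per arm, with no shift in the hazard ratio. These sizes rest on uniform randomization over months 11 to 13 (the maxima on everyone being randomized at one edge), constant hazards, and the planning rates applied to the 24 months after randomization. If the authors meant nominal times, the effect is nil and only the wording is wrong. Either way the sentence for the primary test should match the endpoint. Trial status says the study has not begun, so it can be corrected before any data exist.

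**What to change.** In {20a}, replace the postprocedure window with a rule anchored on randomization:

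- time zero is the date of randomization for every subject;
- all MACEs from that date count;
- subjects without an event are censored administratively at 24 months after randomization;
- Kaplan-Meier rates, their difference and its confidence interval are reported at 24 months after randomization.

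This brings {20a} into line with {12} and Follow-up. It costs one or two sentences of text and needs no extra subjects, visits or data.
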